### Summary:

Breast cancer (BC) is a major health problem and the most prevalent cancer among women. In a substantial proportion of familial cases, germ-line mutations in either BRCA1/2 can be detected. The only proven modality for active risk reduction (rather than passive early detection), is prophylactic surgery - prophylactic mastectomy and oophorectomy. While the majority of Jewish mutation carriers elect to undergo prophylactic oophorectomy at about age 40 years, in Israel only a minority perform prophylactic mastectomy. Another ramification of being a mutation carrier is the emotional stress associated with that discovery. Genetic information has profound implications for mutation carriers. The IBSR (Inquiry-based stress reduction) intervention, developed by Byron Katie, trains participants to reduce their perceived level of stress by self-inquiry of their thoughts and beliefs connected to stressful circumstances or symptoms. This meditative process, named "The Work", enables the participants to identify and question the stressful thoughts that cause their suffering. The core of IBSR is simply four questions and a turnaround, which is a way of experiencing the opposite of what the participant believes. This process is simple, powerful and provides skills for self-inquiry and management of stressful thoughts that can be easily implemented in daily life. Therefore, on the basis of previous data and beneficial observations we postulate that the clinical utility of IBSR mediation program may improve psychological and physical symptoms and quality of life among asymptomatic (oncologically healthy) BRCA1/ BRCA2 mutation carriers. Thus, we will conduct a pilot randomized controlled trial to scientifically investigate the effect of this intervention effects on BRCA1/2 mutation carriers.

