### Study design:

Allocation: Randomized  
Intervention Model: Parallel Assignment

Masking: None (Open Label)  
Primary Purpose: Treatment

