### **Primary Outcome measures:**

**The Ryff scale- Psychological well-being-** quantified using the Ryff questionnaire (84-item). includes six subscales that evaluate: self-acceptance, positive relationships with others, autonomy, control of the environment, personal growth, and goals in life. For each of the dimensions, the score ranges from 14 and 84. Higher scores indicate higher psychological well-being.

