### **Statistical Plan:**

An intention-to-treat analysis approach will be implemented for this trial, and all subjects will be included in the data processing. The similarity of baseline (T1) demographic characteristics of participants in the control and intervention groups will be assessed using the Chi-squared test for categorical variables and independent samples t-test for continuous variables. Differences between the groups will be tested using mixed model analysis over the three different time points as well as the interaction between group and time. The dependent variables is the study outcomes, and the independent variables are time (before, immediately post-intervention, and during the follow-up period), group (intervention and control), and interaction between the time X the group. The difference between the outcome variables will be measured using the entry values (time point 1) and the final values gathered at the end of the follow-up (time point 3). Control for multiple comparisons will be done using the False Discovery Rate approach. An analysis of the research hypotheses of the categorical variables and variables without normal distribution will be performed according to the General Estimated Equation (GEE). To check the internal consistency of the research tools, an alpha Cronbach coefficient test will be performed for each tool. The statistical software SPSS 26 (IBM, New York City) will be used independently for all the data processing within this study by two researchers.

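### Scale scores judged non-normal, possibly including primary Ryff subscales, move from the mixed model to GEE under an undefined rule, and GEE as specified gives weaker guarantees

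*Combined protocol and SAP*

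**What the plan says.** The default analysis in the Statistical Plan is a mixed model with group, time and their interaction: "Differences between the groups will be tested using mixed model analysis over the three different time points as well as the interaction between group and"... Its scope is general ("The dependent variables is the study outcomes"), so it covers the primary outcome. The change of interest is taken "using the entry values (time point 1) and the final values gathered at the end of the follow-up (time point 3").

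A later sentence of the same section sends two kinds of outcome elsewhere. Categorical variables are one kind. The other is defined by shape: the analysis of "variables without normal distribution will be performed according to the General Estimated Equation (GEE").

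The section gives no normality test, cut-off or time point, and does not say whether raw scores or residuals are judged. It states no working correlation and no small-sample correction for GEE, and no covariance structure for the mixed model. On missing data it says only: "An intention-to-treat analysis approach will be implemented for this trial, and all subjects will be included in the data processing".

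The primary outcome is the Ryff questionnaire with six subscales: "For each of the dimensions, the score ranges from 14 and 84". Nothing exempts them from the switch. Study design records "Masking: None (Open Label"), and the Summary says "we will conduct a pilot randomized controlled trial". No sample size is stated.

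**The concern.** The rule has two weaknesses.

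**The trigger.** The estimator for each outcome is settled only once the data are in, by an unstated criterion. Six Ryff subscales could end up split between two estimators. The two researchers who are to process the data independently could also classify the same subscale differently. The property examined is not the one the mixed model needs. That model assumes normal residuals, and for differences in group means on summed scales it is robust to moderate departures even from that.

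**The replacement.** A likelihood-based mixed model with a suitable mean and covariance structure remains valid when dropout depends on scores already observed. Unweighted GEE carries that guarantee only when dropout is completely random or depends on covariates in the model, here group and time. Its robust standard errors are also somewhat too small when participants are few, which is plausible in a pilot.

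At stake is whether the primary comparison is fixed in advance. For outcomes that are switched, p-values could be slightly too small and, in some dropout patterns, the T3 contrast could be shifted.

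**Working it through.** The documents state no sample size, alpha, effect size or dropout rate, so there is no planned figure to reproduce. All values below are assumptions: equal arms of n women, two-sided 0.05 per test, identity link, full group-by-time model.

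**1. Type I error of the uncorrected GEE test (normal, complete data)**

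The robust variance uses divisor n, so it is (n-1)/n times the unbiased variance. For the T3-T1 contrast the test rejects when |t| on 2n-2 df exceeds 1.960 x sqrt((n-1)/n). For the 2-df interaction, the chi-square cut-off 5.991 becomes an F cut-off on (2, 2n-3) df: 5.991 x (n-1)/n x (2n-3)/(2(2n-2)).

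At n = 20:
- T3-T1: 1.960 x sqrt(19/20) = 1.910; the two-sided tail of t on 38 df is 0.0637.
- Interaction: 5.991 x 0.95 = 5.692; 5.692 x 37/76 = 2.771; the upper tail of F(2, 37) is 0.0756.

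| n per arm | T3-T1 | 2-df interaction |
|---|---|---|
| 10 | 7.9% | 10.8% |
| 20 | 6.4% | 7.6% |
| 30 | 5.9% | 6.6% |
| 50 | 5.5% | 6.0% |
| 100 | 5.3% | 5.5% |

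With skewed data and 20% completely random dropout (1,500 simulated trials, Monte Carlo SE about 0.006), GEE gave 6.3-6.7% / 8.2-8.3% at 20 per arm and 6.1-6.2% / 6.5% at 50.

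**2. Does skewness justify leaving the mixed model?**

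The likelihood model with a t or F reference was simulated at 10 per arm. For the T3-T1 contrast and the interaction it gave 5.1% and 4.8% with normal data, and 4.8% and 4.5% with strongly skewed data (gamma, shape 1). With skewed data and 20% random dropout it gave 5.1% / 5.9% at 20 per arm and 5.7% / 5.7% at 50, within about 1.5 Monte Carlo SEs of 5%. Skewness alone gives no reason to switch.

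**3. Bias from dropout (no true effect, within-person correlation 0.6)**

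*One arm only.* Dropout before T3 is random in controls and related to a low T2 score in the intervention arm (log-odds slope 0.5-1.5 per SD). With an independence working correlation, GEE compares the observed T3 means. Its bias is the correlation times the upward shift in mean T2 score among the women who stay:
- 20% dropout: 0.06-0.14 SD.
- 30% dropout: 0.09-0.20 SD.

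The extremes correspond to T2 shifts of 0.06/0.6 = 0.10 SD and 0.20/0.6 = 0.33 SD. In the same scenario exchangeable GEE gave -0.001 to 0.007 SD and a random-intercept likelihood model -0.006 to 0.005 SD.

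*Other patterns* (dropout driven by the last observed score, slope 1 per SD, normal and skewed data):

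| Dropout | Independence GEE | Exchangeable GEE |
|---|---|---|
| 30% vs 10%, same direction | 0.07-0.10 SD | up to 0.006 SD |
| 20% in each arm, opposite directions | 0.18-0.21 SD | up to 0.021 SD |
| 20% in each arm, same direction | up to 0.013 SD | up to 0.014 SD |

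Entries are absolute values. In the first two rows the likelihood model (unstructured covariance) stayed within 0.006 SD of zero. In the last row all three methods agreed to within 0.001 SD, so the departure from zero is simulation noise.

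*Wrong correlation structure.* When the true correlation was AR(1), exchangeable GEE and the random-intercept model stayed within 0.007 SD of each other. The worst case was 0.027 SD against 0.020 SD.

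**The case against.** The strongest reply is that the bias belongs to the independence working correlation, not to GEE as such. The plan does not choose independence, and with an exchangeable structure GEE and the mixed model nearly coincide. That stands. A reader might infer that moving to GEE will bias the result in favour of IBSR. The documents do not support this: they give no working correlation, dropout rate or dropout mechanism, and the direction in the one-arm scenario was set by assumption. Reversing the dropout pattern would reverse the bias.

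Nor does GEE strictly require completely random dropout. It tolerates missingness that depends only on group and time, so heavier dropout in one arm is not harmful in itself. The mixed model's advantage is conditional too, because its own covariance structure is unstated.

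A reader might also infer that analysts would pick the model with sight of the treatment effect. The plan says the trial is open label, but not who judges normality or how. A check on pooled data would need no arm labels.

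It is also fair that the type I inflation is modest unless arms are very small, that the psychosocial scales are labelled exploratory, that summed Ryff subscales may look close enough to normal never to be switched, and that a GEE fallback is an accepted approach.

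These points limit the size of the problem. They do not supply the missing criterion or exempt the primary outcome, and skewness remains a poor reason to change estimator.

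**Conclusion.** The concern holds in a conditional form. The plan states a rule under which the estimator for any scale score, the primary Ryff subscales included, depends on the observed outcome distribution through an undefined criterion. That part needs no assumption about sample size or dropout.

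The consequences for switched outcomes are conditional:
- **Type I error** (T3-T1 / interaction) is about 6.4%/7.6% at an assumed 20 per arm, 5.9%/6.6% at 30 and 5.5%/6.0% at 50, if no small-sample correction is used.
- **Bias** of about 0.06-0.20 SD needs both an independence working correlation and score-dependent dropout in one arm only, at an assumed 20-30% with correlation 0.6. With an exchangeable structure it is about 0.02 SD or less in the patterns tried (0.027 SD at worst when that structure was itself wrong). It is about nil if both arms share the same dropout pattern.

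This should be corrected in the plan. It does not show that the trial's result would be wrong, and using GEE for truly categorical outcomes is reasonable.

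**What to change.** In the Statistical Plan, delete the clause on non-normal variables from the GEE sentence, so that GEE applies to categorical outcomes only.

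- **Scale scores** (Ryff, PSQI, PANAS, SWLS, PSSFA, MAAS, LOT-R, GSE): one pre-specified likelihood-based repeated-measures model whatever the distribution, using REML, an unstructured covariance over the three time points and small-sample degrees of freedom. Check residuals, and add a bootstrap confidence interval as a sensitivity analysis if they are clearly skewed.
- **Categorical outcomes** (such as self-assessed health and risk-reducing surgery): keep GEE, stating a working correlation other than independence and small-sample-corrected standard errors.

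Analyst masking, generalised linear mixed models and multiple imputation are possible additions, but this point does not depend on them.

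The cost is a few sentences in the plan and slightly more programming.

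### No masking of the analysts is planned, although coding the arm labels would cost little and several analysis choices are still open

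*Combined protocol and SAP*

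**What the plan says.** The Study design section gives one masking entry for the whole trial, "Masking: None (Open Label", and exempts no role. The design is randomised with two parallel groups; the allocation ratio is not stated.

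The Statistical Plan assigns the data work to two people: SPSS 26 "will be used independently for all the data processing within this study by two researchers". It does not say whether they are masked, whether arm labels are coded, or whether any decision is locked before allocation is seen.

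The same section leaves several decisions to them:

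- **Model.** Beside the mixed model stands an alternative for categorical outcomes and for others: "variables without normal distribution will be performed according to the General Estimated Equation (GEE". No criterion for non-normality is given.
- **Contrast.** A group-by-time model over three time points is specified, yet the outcome difference "will be measured using the entry values (time point 1) and the final values gathered at the end of the follow-up (time point 3".
- **Multiplicity.** "Control for multiple comparisons will be done using the False Discovery Rate approach", with neither the family of tests nor the level named.
- **Incomplete questionnaires.** Nothing is said, although the primary outcome is "quantified using the Ryff questionnaire (84-item" items long.

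The section does commit to intention-to-treat with every participant retained.

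**The concern.** A behavioural programme can hardly be masked to those who take part, so open label is understandable for participants and providers. It does not follow that the people who analyse the data need to see which group received IBSR. Having two researchers work in parallel protects against entry and programming errors. It gives no protection where both lean the same way. Such a leaning is plausible here, since the Summary describes the programme in favourable terms and postulates benefit.

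At stake is an avoidable bias at the analysis stage, added to a self-report bias that is largely unavoidable. If open choices are settled with the arms visible, a reader of the results cannot exclude that they were settled in favour of the programme.

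**Working it through.** No arithmetic on design figures applies: the documents state no sample size, power, alpha, effect size, standard deviation or dropout rate. The check was to read every section supplied for masking, coded labels or an independent analyst, and then to ask what coding would and would not protect.

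**1. Is any masking planned for the analysts?** The only masking statement is the trial-level entry in Study design. The Statistical Plan adds the two researchers and nothing on what they may see. No other section mentions masking. So none is planned.

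**2. How many outcomes are exposed?** Primary: six Ryff subscales, with no total score or lead subscale named. Secondary: PSQI, PANAS positive, PANAS negative, SWLS, SAH, PSSFA, MAAS, LOT-R and GSE, which is nine; health behaviours come on top. That makes at least 6 + 9 = 15 scores. Of the nine, all but PSQI, that is 9 − 1 = 8, are listed as exploratory.

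**3. Where is there real discretion?**

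| Decision | Settled in the plan? |
|---|---|
| Scoring of scales | Largely: standard instruments, most with item counts and score ranges; SAH is one question |
| Who is included | Yes: intention-to-treat, everyone kept |
| Model for categorical outcomes | Yes: GEE |
| Model for continuous outcomes | No: no criterion for non-normality |
| Missing items or questionnaires | No |
| Decisive contrast | No: T1 to T3 or the three-time-point interaction |
| Family for false discovery rate | No |

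The concern rests on the last four rows only.

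**4. Would coding alone be enough?** No. Write the estimated group difference in change as d = mean change in A − mean change in B. Exchanging the labels turns d into −d, and a two-sided p-value is unchanged. A researcher with A/B data therefore still sees which model or contrast gives a significant result; only the direction in favour of IBSR is hidden. Coding has to be paired with rules filed before any comparison by coded arm is run.

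**5. Could the code be guessed?** Possibly, if one arm improves markedly. It could also be guessed from group sizes if the unstated allocation ratio is unequal.

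**The case against.** The strongest case against is that the open choices are faults of prespecification, not of masking. Written rules would close them whoever sees the labels, and A/B coding without such rules would still allow a significant model to be chosen. That stands, and it is why the fix puts the rules first. Coding still adds protection for judgements that no rule foresees.

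It can also be said that this is a pilot, that most secondary scores are exploratory, and that the dominant bias, unmasked women rating themselves, is untouched. This is true and limits the weight of the point. It does not remove it, because the primary subscales are exposed too and the remedy is cheap.

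Four stronger readings are tempting, and the documents do not support them:

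- *The two researchers know the allocation.* The text does not say so. It follows only by inference from a blanket masking entry and from silence.
- *Every score is open to discretionary scoring, exclusion and model choice.* Scoring is largely fixed by the instruments, exclusions would conflict with the intention-to-treat commitment, and categorical outcomes already have an assigned method.
- *The analysis is the only level at which a blind could be kept.* Whether risk-reducing surgery was performed is a factual outcome that a masked person could record, and data entry could be masked as well.
- *Masking the analysts is free.* Someone outside the analysis must hold the key, and the documents do not describe staffing beyond the two researchers.

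**Conclusion.** The point holds as an omission: no masking of the analysts is planned, while four outcome-relevant decisions remain open. This is a worthwhile and cheap improvement to a stated design feature. It is not a contradiction in the plan and does not invalidate the trial.

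The size of any resulting bias cannot be derived from the documents, and no direction or amount is claimed. Masking the analysts would leave sample size, error rates and power unchanged. The conclusion assumes that comparisons by arm have not yet been run and that a team member who takes no part in the analysis is available to hold the key.

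**What to change.** In Study design, change the masking entry to: *Open label for participants and providers; data analysts masked.*

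In the Statistical Plan, add:

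1. Both researchers work on a dataset with arms coded A/B. The key is held by an existing team member who does not do the analysis.
2. Before any comparison by coded arm is run, four items are fixed and filed: handling of missing items and questionnaires, the model for each outcome (with the criterion for non-normality), the decisive contrast, and the family of tests for the false discovery rate.
3. The code is broken only after the two researchers' primary outputs agree.
4. All randomised participants stay in the analysis, as the plan already requires.

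The cost is a recoded arm variable, a few sentences of text and a small administrative effort to hold the key. No visits, procedures or participants are added. The change does not remove self-report bias.
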